## Abstract

**Background:**

The onset of inadequate behaviors leading to the development of risk factors for chronic diseases is known to occur early in life. An effective program for health promotion should therefore focus on children and their environment, as the starting point for behavior development. The overarching objective of the Program SI! (Salud Integral - Comprehensive Health) is to intervene at the school level, to establish and develop life-lasting habits that will help preserving health during adulthood. The Program SI! comprises five consecutive subprograms according to the five stages of education in Spain, the first being in preschoolers. This study aims to evaluate the efficacy of Program SI! to establish and improve lifestyle behaviors in children (preschoolers aged 3–5 years), their parents, and teachers, and also improving the school environment. A secondary objective is to evaluate improvements in cardiovascular health-related markers (anthropometric parameters, blood pressure, and dietary and physical activity patterns) in these same children.

**Methods/design:**

24 public schools from the city of Madrid (Spain) were allocated through stratified randomization to intervention or control. The intervention schools follow the Program SI!, which provides didactic units, emotions cards, healthy tips, and online resources. The intervention schools integrate the Program SI! into their scholar curriculum organized in four complete weeks during each academic year during the 3 years of preschool education. Control schools follow their normal curriculum. Primary outcomes are 1-year, and 3-year changes from baseline of scores for knowledge, attitudes, and habits (KAH) of children, their parents and teachers in regards to a healthy lifestyle. Secondary outcomes are 1-year, and 3-year changes from baseline in clinical and anthropometric parameters of children.

**Discussion:**

The Program SI! is a long-term health promotion program starting in 3 years old. It incorporates the traditional areas of intervention (diet and physical activity), introducing additional components such as knowledge of the human body and management of emotions to achieve a comprehensive intervention. The Program SI! is designed to be an effective, sustainable health promotion program for the adoption of healthy behaviors from early in life.

**Trial registration:**

Trial registration number: NCT01579708

## Background

Cardiovascular diseases (CVD) are the leading cause of death in the world [1]. It is now apparent that one of main determinants of CVD is the high prevalence of obesity and its comorbidities such as diabetes and hypertension [2]. Obesity also affects children, and it is especially relevant in south European countries [3-6]. The latest data from Spain showed a prevalence of 18.3% obese and 26.2% overweight children (7,659 children, 6–9 years old) [7].

Obesity is mostly a result of inadequate dietary habits and a sedentary lifestyle. It is well known that the development of adequate behaviors start at a very young age [8]. Effective health promotion initiatives directed to young children, should also involve their immediate environment, that is their parents [9,10], and their teachers, and use the school as the center of a multicomponent educational intervention [11-13]. Previous experiences of interventions developed within the school environment and aimed at preventing the development of risk factors have proven to be successful [14]. A recent review on school-based interventions concluded that the most effective programs are those that also include the family and focus on realistic, intermediate objectives such as changes in knowledge, attitudes, and lifestyle habits [15].

The Colombian Initiative for Healthy Heart Study [16], a multi-target educational intervention program based on Sesame Workshop materials aims to change children’s behavior through a comprehensive intervention [17]. It started on preschoolers (3 years old) and involved parents, teachers and the school as a whole. The study included intervention on three components (diet, physical activity, and body and heart) and was evaluated through assessing changes in three domains, knowledge, attitudes and habits (KAH) of children (1,216 children aged 3–5) after 6-months follow up of 14 schools enrolled on a school-based randomized intervention. The investigators found differences of low magnitude, though statistically of note in the knowledge, attitudes and habits (KAH) between the intervention and control groups [17]. Based on the Colombian Initiative, the Program SI! (Salud Integral = Comprehensive Health), was also designed to promoting cardiovascular health from early childhood with the acquisition of healthy habits that will set the basis for a healthier lifestyle during adulthood.

### Intervention program

The Program SI! entails four lifestyle-related components: 1) Diet, 2) Physical activity, 3) Knowledge of the human body and heart, and 4) Management of emotions. While the first two components are directly linked to a healthy lifestyle, the third component is necessary to understand the concept of health, and the fourth aims to prevent the development of behavioral disorders and drug abuse. The Program SI! is based on three domains of behavior development: 1) Knowledge, 2) Attitudes, and 3) Habits. The Program targets four population strata: 1) children, 2) parents, 3) teachers, and 4) the school environment. The Program SI! is implemented in the classroom on four complete weeks during the academic year during every school year (from 2011 to 2014). A summary of the Program SI! intervention including the minimum hours dedicated to each stratum are presented in Table 1. All four components are represented equally in all the activities and materials.

**Table 1 T1:** Summary of the Program SI! Intervention components

**Strata**	**Objectives**	**Intervention activities**	**Intervention materials**	**Minimum hours**
**Children**	Acquiring KAH regarding the 4 components of Program SI!	- Classroom instruction	- Didactic units. Including 7 key activities per unit, and associated resources: Sesame Street audiovisuals, books and games, and cooking workshops, and tales on healthy living	70
		- Health Fair	- Sesame Street Emotion cards	
**Parents**	Improving KAH regarding the 4 components of Program SI!	- Program SI! by [name] (video)	- Informative letters and leaflets	12
		- Health Fair	- Program SI! website	
			- Healthy tips	
**Teachers**	Improving KAH regarding to the 4 components of the PSI!	- Program SI! by [name] (video)	- Training booklet, and associated audiovisual material	30
		- Program SI! capacity building:	- Intranet continuing education tools	
		intensive training for teachers, and SHE Foundation’s liaisons	- Program SI! website	
		- Continuing counseling from SHE Foundation’s staff to the liaisons		
		- Health Fair		
**School**	Improving the school environment in regards of healthy environment	- Program SI! by [name] (video)	- Document of healthy recommendations in schools	20
		- Periodical meetings between principals and SHE Foundation’s liaison	- Program SI! website	
		- Health Fair		

*KAH*, Knowledge, attitudes and habits.

### Aims

The primary aim is to evaluate the efficacy of the Program SI! for preschoolers (3–5 years old) to change the knowledge, attitudes, and habits (KAH) of children, their parents, and teachers in regards to a lifestyle (diet, physical activity, knowledge of the human body, and emotion management) after 3 years of a school-based intervention. The secondary aim is to evaluate the efficacy of the Program SI! for preschoolers to improve cardiovascular health-related risk markers in children, namely anthropometric parameters (weight, height, waist circumference, skinfold thicknesses), and blood pressure after 3 years of intervention. We followed the updated CONSORT Statement for cluster randomized trials [18] to avoid bias in the design and therefore in the reporting results.

## Methods/design

### Study design

The evaluation of the Program SI! in children aged 3 to 5 years (and their parents, teachers, and school environment) was designed as a cluster-randomized controlled open label intervention in the city of Madrid. The unit of randomization, intervention, and analysis is the participating school.

### Sample size calculation

In previous school-based interventions, intra-class correlation (school-group effect) coefficients ranged from 0.05-0.30 for scores that measured academic results [9,19,20]. Taking this range into consideration, and using an estimated intra-class correlation of 0.15, we calculated 20 schools (50 students per level) as sufficient to detect differences of 0.8 in overall scores with a power greater than 80%, and type-I error 0.05 [21]. In anticipation of possible drop outs during the study, a total of 24 schools were randomized, 12 in each group. According to this design, the theoretical sample size for each stratum is presented in Figure 1.

**Figure 1 F1:**
[figure not shown]
Flow diagram of school selection and allocation to intervention.

### Selection of schools and allocation to intervention

During the academic year 2010/11, the number of public schools in Madrid area was 787. In order to homogenize our sample, a series of inclusion criteria were applied to obtain a final subsample with comparable socio-economic characteristics (Figure 1). The study focused only on schools located in the city of Madrid, having full canteen services, and with two or more classrooms per preschool level (needed to attain the 50 students per level used in sample size calculation). This comprised a total of 174 schools. We further gathered data on % immigration and % scholarships, and excluded those schools on the extremes of the distribution. A total of 73 remaining schools were invited to participate on a 1-day meeting where the fundamentals of the Program SI! were presented. A total of 35 schools agreed to participate, from which the final 24 were chosen, excluding larger schools with more than 2 classrooms per level in order to have a similar number of students in each school.

### Randomization process

This trial is based on a hierarchical design, where schools are the experimental units that receive the intervention and therefore are the units that are either randomized to intervention or control group. We randomized the schools using percentage of immigration as stratification factor with four levels (according to quartiles) to ensure that the groups were balanced by differences in cultural background.

### Data collection

#### Primary variables

To assess the impact of the Program SI!, children, parents and teachers participating in the study are evaluated before and after the intervention using an adapted version of the questionnaires developed in the Colombia Initiative for Health Heart Study. These include questions regarding KAH in relation to diet, physical activity and knowledge of the heart and body [17,22]. To further explore the possible changes in the dietary patterns of the children and parents, we used questionnaires previously developed in the studies enKid [23] and Predimed [24] measuring adherence to the Mediterranean diet. We also evaluate possible changes in the physical activity of the children through a physical activity test that was also used in the enKid study [23]. For the evaluation of the fourth component of the program (management of emotions) we use the Test of Emotional Comprehension (TEC) [25]. The number of items of each questionnaire and the assessed component are summarized in Table 2. Finally, to assess the impact of the Program on the school environment, a questionnaire is given to the school’s Principal corresponding to the involvement of the center on Program-related activities. All the evaluation through questionnaires was carried out by trained psychologists.

**Table 2 T2:** Distribution of questionnaires (including number of items) by components, domains, and strata

	**Teachers**	**Parents**	**Children**
**Diet**	KAH (13)	KAH (12)	KAH (10)
		H (14)	H (16)
**Physical activity**	KAH (12)	KAH (11)	KAH (6)
			H (2)
**Human body**	KA (5)	KA (5)	KA (5)
**Emotions**	-	-	TEC (26)

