### Outcomes

Outcome variables of the study for comparing intervention versus control are divided into primary and secondary, depending on the target objective.

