#### Primary outcomes

–Changes from baseline to 1 year and 3 years in the scores of:

○ KAH questionnaires of the children with respect to dietary habits, physical activity, and human body.

○ TEC questionnaire assessing emotion’s management in children.

○ KAH questionnaires of the parents and teachers regarding a healthy lifestyle.

–Changes from baseline to 1 year and 3 years in the overall score for teachers, parents and children.

–Changes from baseline to 1 year and 3 years in the school towards healthier environment based on the recommendations form Program SI!

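### As described, the school-environment primary outcome is measured through involvement in Program activities, so its between-arm contrast would mainly reflect implementation and lean toward the intervention

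*Protocol article*

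**What the plan says.** Under Primary outcomes, the protocol article lists "Changes from baseline to 1 year and 3 years in the school towards healthier environment based on the recommendations form Program SI". The Outcomes section introduces the list with "Outcome variables of the study for comparing intervention versus control are divided into primary and secondary", so this item is meant to be contrasted between arms.

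The instrument is described under Primary variables. Its purpose is "to assess the impact of the Program on the school environment", and the means is a questionnaire for the principal "corresponding to the involvement of the center on Program-related activities". No other measure of the school environment is described. Table 2 sets out the questionnaires for teachers, parents and children only.

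On what each arm receives, the abstract says "The intervention schools integrate the Program SI! into their scholar curriculum organized in four complete weeks during each academic year" and "Control schools follow their normal curriculum". Table 1 has a separate row for the school, with a minimum of 20 hours. It includes a video, regular meetings between the principal and the foundation's liaison, the health fair, a written set of recommendations for schools and the Program website. Study design states that the trial is open label.

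**The concern.** An efficacy outcome has to be something that either arm could improve on. Involvement in the Program's own activities is not of that kind, because it records whether the intervention was taken up. If it is the yardstick for the school environment, intervention schools gain by taking part and control schools have little to report, whether or not anything in the school has become healthier.

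At stake is one item on the primary list. A difference on it could be published as an effect on the school environment when it shows only that the Program was implemented where it was assigned.

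**Working it through.** The plan gives no figure to reproduce here. The check sets the statements side by side and follows what they imply.

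1. **Construct claimed (Primary outcomes).** Movement of the school toward a healthier environment, judged against the Program's recommendations. A control school might meet some of these unprompted.
2. **Construct measured (Primary variables).** The school's involvement in activities related to the Program. This is participation, and it differs from item 1.
3. **Who can score (abstract; Table 1).** The school-level activities and the written recommendations are listed as parts of the intervention. Control schools continue as usual. I take this to mean that control schools are not given the school-level package; the article does not say that they are.
4. **Who answers (Primary variables; Table 1; Study design).** The principal, who knows the allocation and who, in intervention schools, also meets the Program's liaison.

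To see the consequence, split a school's score into P, the items that depend on taking part in the Program, and E, the items that any school can score. Write Δ for mean change from baseline. Then:

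- between-arm contrast = (ΔP intervention − ΔP control) + (ΔE intervention − ΔE control)

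Suppose the Program has no effect on the environment. The second bracket is then zero in expectation, apart from reporting bias. The first bracket is positive as soon as intervention schools take part, because only they are given the activities. The contrast therefore favours the intervention by ΔP intervention − ΔP control.

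The share of P in the questionnaire sets the size:

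- If all items are of type P, the contrast is entirely implementation.
- If none are, this source of bias vanishes and only the unblinded respondent remains.
- The article's description of the instrument points toward P, but the items are not shown and the share is unknown.

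The planned analysis does not repair this. Statistical methods proposes mixed linear models that adjust for baseline and clustering. Participation arises after baseline, so baseline adjustment cannot remove it, and allowing for clustering affects the precision of the contrast, not what is being measured.

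**The case against.** The strongest reply is that the case rests on one loosely worded phrase. Involvement in activities related to the Program could mean school activity in the areas that the Program covers, such as food and exercise, which a control school could also report. The same sentence gives the school environment as the purpose, and the outcome list speaks of a healthier environment. Item content is something that a condensed article leaves to the full protocol. Part of this stands: without the items, nobody can say how much of the score is participation. It does not dispose of the point, because the article does more than stay silent. It states what the questionnaire covers, and that differs from the outcome it is meant to serve.

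A reader might go further and infer that control schools sit at the floor at every visit, so that a positive result is certain. The documents do not support that. They show neither items nor scoring, some recommendations could be met without prompting, and schools invited to take part were shown the fundamentals of the Program before randomization.

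A reader might also add a power argument from the difference of 0.8 in Sample size calculation. That figure concerns overall scores and comes without a standard deviation, so it says nothing about this school-level measure.

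Two further replies limit the weight of the point. Trained psychologists carried out the questionnaire evaluation, so completion was not unsupervised, although this does not blind the principal. And the primary aim, like the abstract's statement of primary outcomes, names the knowledge, attitudes and habits of children, parents and teachers, while Statistical methods analyses scores for the four components. The school item is on the primary list but is not the centre of the trial.

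**Conclusion.** The point holds in a limited form. As the article describes the measure, the between-arm contrast on the school environment would mainly reflect implementation and is biased toward the intervention. The direction is clear and the size cannot be stated.

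The conclusion rests on two assumptions: that the questionnaire covers what Primary variables says it covers, and that control schools do not receive the school-level package in Table 1. If the items turn out to be answerable by both arms without reference to the Program, what remains is a mismatch of wording and an unblinded respondent.

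The severity is moderate. One listed primary outcome is affected. The primary outcomes for children, parents and teachers do not depend on this questionnaire, and nothing in the article lets this item alone establish efficacy.

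**What to change.** - Reconcile the description of the principal's questionnaire under Primary variables with the outcome under Primary outcomes, so that both name the same construct.
- Report involvement in Program activities as an implementation (fidelity) measure, not as an efficacy outcome.
- Base any between-arm comparison of the school environment only on existing questionnaire items that both arms can score identically without reference to the Program, and name those items.
- If there are no such items, remove the school environment from the primary efficacy outcomes.

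The change needs no new data collection, because it only re-tiers and restricts items already put to principals. Keeping to existing items also matters because a new instrument might have no baseline: the Program runs from 2011 to 2014, and the article describes some of the evaluation in the past tense. The downside is one fewer, or a narrower, primary outcome.

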#### Secondary variables

All children participating in the study are evaluated at baseline and 1- and 3-years thereafter. Anthropometric data were obtained according to the guidelines of the International Society for the Advancement of kinanthropometry (ISAK). All examinations were performed by trained examiners in small groups of children. Body weight measurements were taken with a Model 803, Seca® scale (Hamburg, Germany). Mobile stadiometers (model 213, Seca®) were used to measure body height. To establish the cut-offs of obesity we followed the criteria by Cole and co-workers [26,27], therefore different categories were created: thinness grade 3, thinness grade 2, thinness grade 1, normoweight, overweight and obesity. Waist circumference was measured halfway between the lower costal border and the iliac crest using a flexible, nonelastic Holtain tape (Crymych, UK), skinfold thicknesses (triceps and subscapular) are measured using a calibrated Holtain caliper on the right hand side of the body. Percentage of body fat was calculated based on Slaughter equations [28]. Blood pressure was measured twice, with a 2–3 min interval between measurements with Omron Small arm cuff (arm circumference 17–22 cm adapted for children, model M6, Omron® CS2). The child is seated in relaxing conditions with the right arm semi-flexed at heart level. Normal blood pressure and hypertension is defined according to the criteria of the Fourth Report on the Diagnosis, Evaluation, and Treatment of High Blood Pressure in Children and Adolescents [29].

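### If all three preschool levels are enrolled, the 3-year comparison of children and parents mixes 1, 2 and 3 years of exposure and does not estimate the effect of 3 years of the programme

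*Protocol article*

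**What the plan says.** - **Population.** The Study design section describes "The evaluation of the Program SI! in children aged 3 to 5 years (and their parents, teachers, and school environment"). The sample size is given as 50 students per level. The school selection section admits schools "with two or more classrooms per preschool level (needed to attain the 50 students per level used in sample size calculation").
- **Programme.** The abstract says the programme is "organized in four complete weeks during each academic year during the 3 years of preschool education". The Intervention program section dates it "during every school year (from 2011 to 2014"), which is three school years.
- **Aim.** The primary aim is efficacy on knowledge, attitudes and habits "after 3 years of a school-based intervention".
- **Assessment.** Under Secondary variables, "All children participating in the study are evaluated at baseline and 1- and 3-years thereafter". Primary outcomes uses the same times, for example "Changes from baseline to 1 year and 3 years in the overall score for teachers, parents and children".
- **Analysis.** Statistical methods names mixed linear models that adjust for baseline variables and clustering. It mentions neither preschool level nor years of programme received.

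Nothing in the article limits the 3-year comparison to children who entered at the first level.

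**The concern.** Each statement is reasonable alone, but together they do not fit. A programme confined to three preschool years can be received for three years only by a child who starts at the first level. If children at all three levels are enrolled and all are followed to three years, two thirds of them (with equal levels) cannot have had the exposure named in the primary aim. They are also measured one or two years after leaving preschool. Their parents are in the same position.

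The meaning of a primary time point is at stake. A modest pooled 3-year difference could reflect a weak programme, or an effective one that most participants received for only one or two years. Without separation by entry level, the reported 3-year result could not distinguish the two.

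**Working it through.** **1. The plan's own figure.** Inputs from Sample size calculation: 20 schools (10 per arm), m = 50, intra-class correlation (ICC) 0.15, difference 0.8, alpha 0.05 (taken as two-sided), power above 80%.

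- Design effect = 1 + (50 − 1) × 0.15 = 8.35.
- Effective n per arm = 10 × 50 / 8.35 = 59.9.
- The SD of the overall score is not given. If 0.8 is in SD units, power is 98.5% (noncentral t, 18 df). Power of exactly 80% would need an SD of about 1.48.

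The claim of more than 80% is consistent with this, but the figure cannot be reproduced uniquely.

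**2. Exposure at the 3-year visit, if all levels are enrolled.**

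| Level at baseline | Approx. age at baseline | Maximum programme years | Time since preschool at 3 years |
|---|---|---|---|
| First | 3 | 3 | none |
| Second | 4 | 2 | about 1 year |
| Third | 5 | 1 | about 2 years |

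With equal levels, mean exposure is (3 + 2 + 1)/3 = 2.0 years. This step is arithmetic and needs no assumption about effect.

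**3. Pooled effect relative to the full effect.** This step needs a dose-response, which the article does not give. The factor f is the mean over levels of the share of the 3-year effect reached.

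- No dose-response and no fading: f = 1.00.
- Saturating (60%, 85%, 100% after 1, 2, 3 years): 2.45/3 = 0.82.
- Proportional to years: (1/3 + 2/3 + 1)/3 = 0.67.
- Proportional, with a quarter lost one year after leaving and half lost two years after: (0.167 + 0.50 + 1)/3 = 0.56.
- Effect only after three full years: 1/3 = 0.33.

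**4. Power of the pooled 3-year comparison.** 24 schools, 150 children per school, ICC 0.15. Design effect = 1 + 149 × 0.15 = 23.35, and effective n per arm = 12 × 150 / 23.35 = 77.1. Power is from a noncentral t with 22 df and noncentrality f × effect / √(2/77.1). Two full effects are shown: 0.489 SD, chosen because it gives exactly 80% power in first-level entrants alone, and 0.8 SD, if the plan's difference is in SD units.

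| f | Power, full effect 0.489 SD | Power, full effect 0.8 SD |
|---|---|---|
| 1.00 | 83% | above 99% |
| 0.82 | 66% | 97% |
| 0.67 | 49% | 89% |
| 0.56 | 36% | 75% |
| 0.33 | 16% | 35% |

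**5. Cost of using first-level entrants only.** Effective n per arm = 12 × 50 / 8.35 = 71.9. The detectable difference at 80% power is 2.93 × √(2/n), where 2.93 is the noncentrality needed at 22 df.

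| ICC | 50 per school | 150 per school | Increase |
|---|---|---|---|
| 0.05 | 0.314 SD | 0.284 SD | 11% |
| 0.15 | 0.489 SD | 0.472 SD | 3.6% |
| 0.30 | 0.671 SD | 0.661 SD | 1.5% |

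At ICC 0.15, first-level entrants alone give more power than the pooled sample whenever f is below 0.472/0.489 = 0.97. The calculation uses one school-level correlation for both cohort sizes.

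**The case against.** The strongest objection is that the article never says the children are 3 to 5 at baseline. A single cohort entering at 3 and passing through ages 3 to 5 also fits a programme described as starting at age 3, running through three preschool years and assessed at baseline, 1 and 3 years. On that reading the problem disappears. Figure 1, which holds the theoretical sample size per stratum, is not available here. This objection stands, and the point is conditional for that reason. Two things favour the all-levels reading: the counting of students and classrooms per level, and the Background's use of ages 3–5 for participants in a study followed for only 6 months, where it can hardly mean ages passed through.

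Second, a reader might infer that the 3-year result would be biased or uninterpretable. The article does not support that. Schools are the unit of randomisation, intervention and analysis, so the pooled contrast validly estimates the effect of a school running the programme for three years, averaged over levels. The wording of the aim can bear that meaning. The issue is which effect is being estimated.

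Third, a reader might take dilution, or a fall in power to 49%, as established. Dilution needs a dose-response or fading, neither of which is documented. The 49% starts from an effect back-solved to give 80%; from 0.8 SD the same dilution leaves 89%.

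Fourth, a reader might infer heavy loss among older entrants. The article does not say that children finishing preschool leave the school or the study. Nor does it say whether they go on to the next of the five subprogrammes. If they do, their 3-year contrast would not be the preschool programme alone.

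Finally, by-level terms are often left to an analysis plan, and their absence here is not the complaint. The complaint is that the stated population, programme length and follow-up do not match the stated aim.

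**Conclusion.** The point holds conditionally. If all three levels are enrolled at baseline, the 3-year child and parent comparison pools participants who can have had at most 1, 2 or 3 years of the programme, and it does not estimate the effect of three years of exposure. That mixing follows from the article's own figures.

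The pooled effect is probably smaller than the full-exposure effect: about 67% of it with equal levels and benefit proportional to years, and 33% to 100% across the shapes tried. The loss of power cannot be fixed from the article, because neither the SD of the score nor the dose-response is given.

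The 1-year outcomes are unaffected, since every level can receive one year. The teacher and school-environment outcomes are unaffected too. If only first-level children were enrolled, there is no mixing and one clarifying sentence is enough.

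**What to change.** State which preschool level(s) are enrolled at baseline. If only the first, say so; nothing else changes.

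If all three are enrolled:

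- Include entry level and a treatment-by-level term in the 3-year mixed model for children and parents.
- Take the 3-year effect in first-level entrants and their parents, analysed as randomised, as the answer to the aim of efficacy after three years.
- Report the all-levels 3-year effect as a secondary, school-level estimate.
- Leave the 1-year, teacher and school-environment outcomes as they are.

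The change is to wording and model specification and needs no new data. The first-level cohort is the 50 per school already used in the sample size. The price is a detectable 3-year difference about 4% larger at ICC 0.15 (0.489 against 0.472 SD with 24 schools), about 11% larger at 0.05 and 1.5% larger at 0.30.
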